#### Analysis

Intention-to-treat analyses and per protocol analyses will be performed. Reporting of the results will follow CONSORT recommendations [75, 76]. First, the two groups will be compared in order to verify that there are no significant differences between them at baseline using samples t-tests for continuous distributed variables and chi-squares test of independence for categorical to confirm that they are comparable after randomization.

The intention-to-treat principle will be used when analyzing primary and secondary post-treatment data and data collected at the 3- and 12-month follow-ups using mixed effect models with full information maximum likelihood estimation. This method has been recommended for its flexibility over repeated-measures ANOVAs to handle missing date more appropriately [109].

Within and between-group changes will be computed calculating standardized effect sizes (Cohen’s d). Cohen’s d is calculated by dividing the differences between means by the pooled standard deviation [110]. An effect size of 0.20 is considered to be small, of 0.50 to be moderate, and 0.80 and above to be large [110].

Per protocol analyses (compliers only analysis) will also be conducted. Despite this procedure suffers from selection bias, it can help to draw conclusions about the maximum treatment efficacy in patients who comply fully with the treatment [111].

As the trial is still in execution, the state of the art regarding analytic methodology for RCT will be reviewed before analyzing the data, thus variations in the selection of the most appropriate analytic procedures may occur.

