## Methods/Design

### Study design

A two-armed simple-blinded randomized controlled trial will be conducted. Participants will be randomly allocated to one of two conditions: a) EmotionRegulation and b) TAU. Randomization will be stratified by primary diagnosis. Block randomization will be performed within each strata in order to ensure all primary diagnoses are equally represented across conditions. The study will be conducted following the CONSORT statement (Consolidated Standards of Reporting Trials, http://www.consort-statement.org) [75, 76] and CONSORT-EHEALTH guidelines [77]. Participants will be assessed at pre- and post-treatment, and at 3- and 12-month follow-ups. The study flowchart is shown in Fig. 1.

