### Study population

The clinical trial will be conducted in the Mental Health Department of the Provincial Consorcio Hospitalario in Castellon and the University Hospital La Ribera in Valencia (Spain). Participants will be adult outpatients from specialized care who attend mental health units to seek psychological and/or psychiatric treatment. Participants will be recruited by clinical psychologists and psychiatrists working in these centers, until the required sample is complete. In order to facilitate the selection of participants in the study, both clinical psychologists and psychiatrists will be given a sheet containing the eligibility criteria.

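### The planned baseline significance tests cannot confirm comparability, and the stated mixed model names neither the baseline score nor the diagnosis strata used in randomisation

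*Protocol article*

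**What the plan says.** Under Study design, the protocol article states: "Randomization will be stratified by primary diagnosis". It adds: "Block randomization will be performed within each strata in order to ensure all primary diagnoses are equally represented across conditions". Eligibility criteria lists nine diagnoses. Table 3 has BAI and BDI-II measured at baseline and at every later assessment.

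Under Analysis, the first step is that "the two groups will be compared in order to verify that there are no significant differences between them at baseline". The tools are t-tests and chi-square tests, and the purpose given is "to confirm that they are comparable after randomization". Outcomes are then analysed "using mixed effect models with full information maximum likelihood estimation". The intention-to-treat principle is applied "when analyzing primary and secondary post-treatment data and data collected at the 3- and 12-month follow-ups". No covariate is named, the strata are not mentioned, and the text does not say whether baseline enters as a covariate, as a repeated outcome or not at all. The section ends by leaving the method open: "thus variations in the selection of the most appropriate analytic procedures may occur".

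**The concern.** Two things are at issue, of different standing.

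The first is a stated error. When allocation is random, differences in variables measured before allocation are due to chance. A significant test does not show that randomisation failed, and a non-significant one does not show that the arms are balanced on what matters. The tests therefore cannot serve the purpose the article gives them.

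The second is conditional. Blocking within diagnosis removes between-diagnosis variation from the real sampling variance of the treatment difference. A model without diagnosis leaves that variation in the residual, so its standard error is too large. Leaving out the baseline score gives up precision in a trial that, after its expected dropout, has little to spare. Both variables are already collected.

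**Working it through.** **1. The plan's own figure.** Inputs from Sample size: d = 0.40, one-sided alpha 0.05, power 0.80, dropout about 30%, 100 per condition.

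- n = 2 × (1.645 + 0.842)² / 0.40² = 77.3, so 78 per arm before dropout.
- 78 × 1.30 = 101.4, close to the stated 100. Dividing instead, 78 / 0.70 = 111.4, so 112.

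The stated 100 is reproduced only by the first inflation. That is a separate matter; what counts here is that 100 × 0.70 = 70 completers per arm.

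**2. Baseline tests.** The chance of at least one significant result among k independent tests is 1 − 0.95^k: 0.23 for k = 5, 0.40 for k = 10, 0.54 for k = 15. The article gives no k, and the baseline scales are unlikely to be independent, so these figures are illustrative.

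**3. Baseline score and power.** Power = Φ(d / √(2v/70) − 1.645). The variance factor v is 1 for the post score alone, 1 − ρ² with baseline adjustment, and 2(1 − ρ) for an unconstrained change from baseline. Example at ρ = 0.5: √(2 × 0.75/70) = 0.1464; 0.40/0.1464 − 1.645 = 1.087; Φ = 0.86. The baseline-to-post correlation ρ is not in the article, so a range is assumed.

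| ρ (assumed) | Post score only | Change from baseline | Baseline-adjusted |
|---|---|---|---|
| 0.3 | 0.765 | 0.64 | 0.80 |
| 0.5 | 0.765 | 0.765 | 0.86 |
| 0.7 | 0.765 | 0.92 | 0.95 |

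A mixed model with baseline as a repeated outcome and a common baseline mean across arms recovers most of the last column.

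**4. Strata.** Simulation: 200 participants, nine equally likely strata, blocks of 4, 30% random dropout, 4,000 runs per setting. Number of strata, block size and variance explained by diagnosis are assumptions. Baseline score is in neither model.

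| Variance explained | Model SE without strata | True SD of estimate | One-sided error without strata | Power without → with strata |
|---|---|---|---|---|
| 0% | 0.1691 | 0.1669 | 4.8% | 0.756 → 0.750 |
| 5% | 0.1693 | 0.1656 | 5.05% | 0.764 → 0.770 |
| 10% | 0.1690 | 0.1644 | 4.45% | 0.769 → 0.794 |
| 20% | 0.1687 | 0.1572 | 3.6% | 0.767 → 0.829 |

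At 20%, 0.1687/0.1572 = 1.07. Simulation error is about 0.3 percentage points on the error rates (√(0.05 × 0.95/4000)), about 0.7 on power and about 1% on the SDs, so the 0% and 5% rows show little or nothing. Without dropout the 20% ratio is 0.1413/0.1285 = 1.10, near the theoretical 1/√0.8 = 1.12. Dropout weakens the effect because it disturbs the balance within strata.

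The gains in steps 3 and 4 should not be added: once baseline score is in the model, diagnosis is likely to explain less of what remains.

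**The case against.** The strongest reply is that most of this rests on silence. A journal article condenses the protocol, covariate lists usually sit in the analysis plan, and that plan is not shown. This stands in large part, and it rules out several stronger readings.

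- **That the tests replace adjustment.** A reader might infer this because they are the only stated use of baseline differences. The article does not say so, nor that no covariates will be used.
- **That covariates will be picked from the test results.** The tests have one stated purpose, comparability, and no modelling decision is tied to them.
- **That false positives will be inflated.** The direction is the reverse: intervals too wide and type I error below nominal, and only if diagnosis predicts outcome and is left out. The article gives no BAI or BDI-II severity by diagnosis.
- **That power is certainly lost.** The 76% belongs to a comparison of post scores alone. A mixed model may take baseline as a repeated outcome. The sentence on the model names only post-treatment and follow-up data, so the question stays open either way.
- **That centre must be adjusted for.** Recruitment takes place in the "Mental Health Department of the Provincial Consorcio Hospitalario in Castellon and the University Hospital La Ribera in Valencia", but randomisation is stratified by diagnosis only, so the argument from stratification does not extend to centre.

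The reply does not reach the baseline tests themselves. They are stated in the article, with a purpose they cannot meet, and an unseen analysis plan does not change that.

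One caution runs the other way. Under Recruitment, participants are randomised and then complete the remaining instruments. If BAI or BDI-II are filled in once allocation is known, differences in them need not be pure chance. A non-significant t-test would not settle that either.

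**Conclusion.** The point holds in a limited form. The baseline tests are a stated mistake, though one of reporting: as written they do not alter the treatment estimate.

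The model as stated names neither baseline score nor the randomisation strata. Run that way, it would be conservative and less powerful than it could be. Under the assumptions shown, leaving out diagnosis costs about 7% in standard error and 6 points of power (0.767 against 0.829) at 20% explained variance, and nothing at 0%. Leaving out baseline costs about 3 to 19 points of power for ρ from 0.3 to 0.7, and much less if baseline is already a repeated outcome with a common mean. The validity of the trial is not in question.

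**What to change.** Replace the baseline tests with a descriptive table by arm (means and SDs, counts and percentages, no p-values). State in advance that each mixed model includes:

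- the baseline score of the scale analysed, either as a covariate or as a repeated outcome with a common mean across arms;
- primary diagnosis as a fixed factor, with sparse strata merged by a rule set before unblinding.

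Confirm that BAI and BDI-II are completed before allocation is known. Adjustment for centre is optional.

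The cost is wording in the analysis plan. The variables are already collected, no further participants are needed, and the change can be made before any outcome data are analysed. If diagnosis turns out to explain nothing, including it costs almost nothing: 0.756 against 0.750 in the simulation, which is within simulation error.

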
These modules are sequential, in order to move through the program step by step. The program duration can vary among the users, and it is estimated that for most participants the duration will be 18 weeks. During the study, EmotionRegulation will be accessible only to participants in the online intervention group. Participants will be allowed to use the program at any time they want during the trial period. See Table 2 for other functionalities in EmotionRegulation.

**Table 2 Tab2:** Other functionalities in EmotionRegulation

a) Assessments: The program allows the pre-, post- and follow-up instruments to be completed online.	
b) Module self-assessments: Each module ends with a short list of multiple-choice questions that allow participants to assess their understanding of the module and help them to decide whether they need to review its contents.	
c) Automatic e-mails with reminders when participants have not accessed the program in the past 15 days.	
d) Suicide risk alarms: Therapists receive warnings of participants with high risk of suicide (when participants answer questionnaires that include items assessing high suicide risk)	
e) Post-module questionnaires: Each module includes three brief questionnaires (OASIS, ODSIS and PANAS) to evaluate anxiety, depression and positive/negative affect after each treatment module. Participants are able to monitor these scores in the feedback section through the ‘How am I?’ button.	
f) Printable documents: Each module contains several printable documents (PDF) with summaries and self-monitoring sheets that participants are encouraged to use to practice the skills and strategies.	

Participants in the EmotionRegulation condition will be allowed to maintain medication if there are not changes and/or increases but will not be allowed to receive another psychological treatment during the study period. Failure to fulfill these criteria will result in the participant’s data being excluded from data analysis.

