#### Sample size

The data from an RCT using the UP yielded between-group effect sizes of 0.56 for anxiety and 1.11 for depression, as measured with the BAI and BDI-II, respectively [30]. As we aim to compare the intervention with a TAU group, the results of a meta-analysis comparing CBT transdiagnostic treatments versus TAU have also been considered in the estimation of the expected sample size [106]. This meta-analysis reported a medium post-treatment effect size of 0.44 for depression and of 0.34 for anxiety between transdiagnostic treatment protocols vs. TAU conditions. The type of support we provide in this intervention (contact with researchers before, during and after the treatment period) has also been taking into account when estimating the expected sample size, as defined in a previous meta-analysis focused on Internet-based psychological treatments for depression [107]. Based on a power of .80 in a one-tailed test, an alpha of .05, and an estimated drop-out rate of around 30 % [65, 108] we need a sample size of 100 per condition to detect a post-treatment effect size of 0.40 (Cohen’s d) between both groups. Therefore, the total sample size was determined at 200.

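### The compliers-only analysis cannot support a conclusion about maximum treatment efficacy: report it as descriptive and add a randomisation-based complier effect

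*Protocol article*

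**What the plan says.** The Analysis section makes intention to treat, with mixed models fitted by full information maximum likelihood, the analysis of primary and secondary outcomes at post-treatment and both follow-ups. It then adds: "Per protocol analyses (compliers only analysis) will also be conducted". It admits that this procedure is subject to selection bias, but in the same sentence says that "it can help to draw conclusions about the maximum treatment efficacy in patients who comply fully with the treatment".

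Three other places bear on the point:

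- **Access.** The Interventions section states that during the study "EmotionRegulation will be accessible only to participants in the online intervention group". The Ethics section offers the program to TAU patients only once the study is over.
- **Exclusions.** Eligibility criteria and Interventions remove from analysis those experimental-arm patients whose medication is changed or increased. Interventions does the same for those who take up another psychological treatment. Neither section gives a matching rule for TAU.
- **Planning figures.** The Sample size section aims to "detect a post-treatment effect size of 0.40 (Cohen’s d) between both groups" and assumes "an estimated drop-out rate of around 30" per cent.

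The article does not define a complier, and it does not say which TAU patients serve as the comparison group. A condensed article may leave such detail to the full protocol or analysis plan, so neither gap is counted as a fault here.

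**The concern.** The fault is in the inference, not in running the analysis. A conclusion about efficacy in people who comply fully needs a comparison with TAU patients who would also have complied. Because TAU patients have no access to the program, none of them can show compliance with it, and the right comparison group cannot be picked out. Whichever TAU patients are used, the two sides are no longer balanced by randomisation. The difference then combines the effect of the program with any difference in outlook between people who persist and people who do not. The exclusions that apply only to the experimental arm would add to the imbalance.

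Admitting selection bias does not repair this, since the article offers neither a correction nor a bound. At stake is a supplementary estimate that could be read as the program's efficacy under full use when part of it is prognosis.

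**Working it through.** **Inputs from the article.** Target d = 0.40; 100 patients per condition; drop-out about 30%; no TAU access during the study.

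**Inputs assumed.** The share who comply, p, and the prognostic advantage of would-be compliers over the others under TAU, g in SD. The article gives neither. The range is p = 0.5 to 0.8 and g = 0.2 to 0.5, with p = 0.7 as the working value. The 30% in the Sample size section is drop-out; it is not a non-completion rate, so p = 0.7 cannot be read from it.

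**The plan's own figure.** The article gives no figure for the compliers-only analysis. Its 100 per condition is used below only as an arm size. That figure is not itself reproduced: a one-sided 5% test with 80% power at d = 0.40 needs 78 per arm, and 78 / 0.70 rounds up to 112. This is a separate matter, and the argument here does not rest on it.

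**Bias of compliers against all TAU.** Score benefit as positive, and let c be the true effect in compliers. Under TAU, set the mean of would-be compliers to 0 and that of the others to -g.

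- Mean of experimental-arm compliers: c
- Mean of all TAU patients: p × 0 + (1 - p) × (-g) = -(1 - p)g
- Expected contrast: c + (1 - p)g, so the bias is (1 - p)g

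| p | g = 0.2 | g = 0.3 | g = 0.5 |
|---|---|---|---|
| 0.5 | 0.10 | 0.15 | 0.25 |
| 0.7 | 0.06 | 0.09 | 0.15 |
| 0.8 | 0.04 | 0.06 | 0.10 |

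At p = 0.7, g = 0.3 to 0.5 gives 0.3 × 0.3 = 0.09 to 0.3 × 0.5 = 0.15 SD. Relative to 0.40 that is 0.09/0.40 = 23% to 0.15/0.40 = 38%. If g were negative, the bias would run the other way.

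**Simulation.** 20,000 trials, 100 per arm, complete data, p = 0.7, g = 0.3.

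| True complier effect | Compliers v all TAU | One-sided 5% rejection, compliers v all TAU | ITT/p |
|---|---|---|---|
| 0 | 0.09 | 14.3% | 0.00 |
| 0.40 | 0.49 | 93.0% | 0.40 |

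With no true effect, intention to treat rejected in 5.3% of trials.

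**Complier average causal effect.** Non-compliance is one-sided, so if non-compliers gain nothing from the offer, ITT = p × c and c = ITT/p. For c = 0.40 (a value taken for scale) and p = 0.7, ITT = 0.28 and 0.28/0.70 = 0.40.

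**Precision.** SE(ITT) = √(2/100) = 0.141. SE of ITT/p is about 0.141/0.7 = 0.202, which is 1/0.7 = 1.43 times as large. At p = 0.5 it is 0.141/0.5 = 0.283. These values assume complete data.

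**If non-compliers gain h from partial use.** ITT/p = [p × c + (1 - p) × h]/p. With c = 0.40 and p = 0.7:

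- h = 0.1: (0.28 + 0.03)/0.7 = 0.44
- h = 0.2: (0.28 + 0.06)/0.7 = 0.49

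**The case against.** The best reply is that the article is open about the problem. Intention to treat is the main analysis, the compliers-only result is an addition, selection bias is admitted and the wording is hedged. None of the stated aims depends on this result. All of that stands, and it limits the point to how a supplementary analysis is interpreted. A reader might infer that the trial will rest its efficacy claim on the compliers-only figure; the text does not say so.

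A reader might also infer that people who finish all the modules will be set against every TAU patient, that 70% will finish, and that the result must be too favourable. The article states none of these. It defines neither a complier nor the TAU comparison group, gives no completion rate, and offers nothing on the prognosis of compliers. The loss of randomised comparison follows from the lack of TAU access whatever the definitions; the size and direction of the bias do not.

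The third reply is that the alternative is neither free nor free of bias. The modules are sequential, so people who stop early may have done several, and the Support section gives the arm weekly calls and two text messages a week. A gain of 0.1 to 0.2 SD in non-compliers puts an error of 0.04 to 0.09 into ITT/p at p = 0.7, which reaches the lower end of the bias criticised above. This stands. It is why the complier effect belongs beside intention to treat as a supplementary analysis with sensitivity checks. It does not rescue the inference that the article draws.

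Finally, the article says that its analytic methods will be reviewed before the data are analysed, so a complier model is not ruled out. That makes the change easy to adopt, but the inference stands as written until it is changed.

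**Conclusion.** The point holds as a fault of interpretation in a supplementary analysis. A compliers-only contrast does not estimate maximum efficacy when would-be compliers in TAU cannot be identified, and conceding the bias does not change that. At 70% compliance, a prognostic gap of 0.3 to 0.5 SD and comparison with all TAU patients, the bias is 0.09 to 0.15 SD. Over the wider assumed range it is 0.04 to 0.25 SD. Every one of those conditions is an assumption, and an upward direction requires compliers to have the better prognosis. The main intention-to-treat conclusion does not depend on the compliers-only result. The change is worth making, but it is not critical to the trial.

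**What to change.** 1. Drop the inference about maximum efficacy and report the compliers-only result as descriptive. This is a change of wording and should be made even if the next step is declined.
2. Add, as a supplementary analysis, a complier average causal effect with randomised arm as the instrument, and fix the definition of a complier before data review.
3. Keep the outcomes of all randomised patients in that analysis. The data exclusions in Eligibility criteria and Interventions, which apply only to the experimental arm, must first be reconciled with the intention-to-treat statement in Analysis.
4. As sensitivity analyses, vary the completion cut-off and allow directly for a partial benefit in non-compliers, for example 0.1 to 0.2 SD.
5. Leave intention to treat as the main analysis.

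**Cost.** No new patients, visits or instruments; a little more analysis work; a standard error about 1.4 times that of intention to treat at 70% compliance and twice at 50% (1/0.5); and reliance on the exclusion restriction, which is open to doubt here and is the reason for step 4. The article reports that the trial is still recruiting, so these choices can be set down in advance.

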## Discussion

This study has several aims. The first is to provide data from a RCT about the effectiveness of a transdiagnostic Internet-based protocol for the treatment of ED in a sample of participants from specialized care in the Spanish public mental health system, compared to TAU. Second, whether the treatment may temper the psychological vulnerability by analyzing its effect on psychological higher-order dimensions (neuroticism/behavioral inhibition and positive affect/behavioral activation) will be studied. The third aim is to study the acceptability of this online program by patients in an ecological setting (public specialized care in Spain).

The advantages of a transdiagnostic Internet-based protocol are two-fold. First, a wide range of ED can be treated with a single protocol, reducing the costs associated with disorder-specific protocols and contributing to solving the problem of comorbidity and NOS diagnoses, as the protocol focuses more on the common pathological processes than on any specific disorder and/or symptomatology. Second, Internet-based protocols can help to disseminate CBT evidence-based treatments, so that more people can benefit from them. This study will provide additional data about the transdiagnostic perspective proposed by Barlow [20], as well as data on the combination of a transdiagnostic perspective and the use of ICTs.

In addition, this study has various strengths. First, this is the first RCT of transdiagnostic Internet-based psychotherapy in specialized care in our country. Positive results achieved with this protocol may have an important impact, since protocols of this type could help to decrease the saturation of the public mental health system, reducing costs and contributing to a general improvement in the public mental health services in our country (for example, reductions in waiting lists, hours of clinical assistance and hours of face-to-face treatment; a higher number of patients who receive psychological treatment; etcetera). Second, the online protocol combines the transdiagnostic cognitive-behavioral principles (psycho-education about emotions, enhancement of cognitive flexibility, interoceptive and situation-based emotion exposure) with components of acceptance and emotion regulation for the treatment of ED. The data obtained with this protocol can help us to understand the psychopathology of these mental disorders. And third, even though transdiagnostic Internet-based protocols are thought to treat different ED, most of the existing studies exclusively target anxiety disorders [25, 26, 73], and others have used open-trial designs [28, 74] and do not contemplate either the diagnosis of obsessive-compulsive disorder or NOS diagnoses [29] or they focus on a smaller number of ED [29]. We consider that this study broadens the current literature about transdiagnostic Internet-based protocols as it is designed for a wide range of anxiety and depressive disorders. Combining the advantages of both a more inclusive transdiagnostic intervention and an Internet-based delivery format may broaden the scope of evidence-based treatments among the population in need. Moreover, the population in which the study is being conducted, that is, patients who attend a variety of public specialized care settings across Spain, can help to draw conclusions about the external validity of the intervention.

Finally, a number of potential limitations should be indicated. First, dropout rates are expected to be high (around 30 %) [67, 110]. Efforts to maintain these drop-out rates below this percentage will be made by providing human support (before, during, and after the intervention) and ICT-support (for example, emails and mobile phone text messages). Second, negative attitudes towards Internet interventions by both clinicians and patients may affect recruitment as well as dropout rates. To minimize the effect of negative attitudes, the nature and characteristics of the intervention will be explained to clinicians involved in the trial. Moreover, for this purpose they will be given a handbook with relevant information about the study (for example objectives of the study, study design, and characteristics of the intervention). In order to increase participant’s credibility, prior to enrollment they will be given a sheet with relevant information concerning the characteristics and objectives of the study, and other issues related to ethics, voluntary participation and confidentiality of the data. Finally, other difficulties could be problems with recruitment, as many people who attend public mental health units do not have access to the Internet at home.

